### Interventions

Participants included in this study will receive 6 treatment sessions (one per week), with a corresponding evaluation before the start of each treatment session. In addition, the participants after completing the last treatment session, will receive post-treatment assessments; at one week, at one month, at 3 months and at 6 months.

### Dry needling of myofascial trigger points

To perform the dry needling procedure, patients should be placed on: their healthy or good side for infraspinatus and deltoids muscle; supine decubitus for subscapularis muscle; and prone decubitus for upper trapezius muscle. The physiotherapist will treat each MTrP that have previously been located in the muscles: upper trapezius, infraspinatus, subscapularis and middle deltoid.

After this, a 0.30x40mm monofilament needle (AGUPUNT, APS®) will be inserted towards the muscle mass. Said needle should be inserted into and extracted from the muscle using the “fast in and fast out” technique [23]. Needle insertion will be repeated 12 times in each muscle, the dry needling procedure being similar to that used by Hong [23, 24]. At most one MTrP (the one producing most pain) in each of the muscles will be needled. If no MTrP is found during muscle palpation, the needling procedure will not be performed on that muscle.

Meanwhile, the control group will receive the same treatment but using 0.30x30mm sham needles (Streitberger Placebo - needle®, Asiamed), which have been used before in another study [25].

Participants in both groups, will receive the same information about the sensations of dry needling procedure. They will be informed, at the beginning of the technique, that they may or may not feel the introduction of a needle through the skin. This will be related to the area of the body where the puncture is performed and according to the sensitivity of the subject. Afterwards, they will feel as the physiotherapist manipulates the needle with his hand repeatedly. In addition, participants should communicate to the physiotherapist the sensations they notice during the performance of the technique.

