### Participants

From the town of Alcalá de Henares (Madrid), aged between 18 and 65 years with chronic mechanical shoulder pain of unspecific origin, lasting at least 3 months and provided they give their consent after being informed about participation in the study. The recruitment of participants will be conducted via email for University of Alcalá workers and students and by placing posters in a number of social and sports centres around the city of Alcala de Henares, where information about the study and contact information will be provided. Subsequently, a first telephone interview will be conducted to clarify any doubts of the participants, and the first screening for inclusion in the study will be carried out.

Participants’ personal data will be numerically coded and stored in a computer database, which may only be accessed to by the physiotherapist in charge of participant randomization and blinding.

Informed consent, as well as all study information will be emailed to the participants. Subsequently, prior to data collection and baseline measurement, participants should sign the informed consent, which could be revoked at any time during the intervention.

Inclusion criteria:Chronic mechanical shoulder pain of unspecific origin lasting at least 3 months.Aged between 18 and 65 years.Presence of active trigger points or areas of mechanical hypersensitivity in the muscles to be treated (upper trapezius, infraspinatus, subscapularis and middle deltoids) with pain reproduced in one or more muscles.

Participants will be examined for the presence of active trigger points in the muscles selected by a clinician with more than 10 years of experience in the treatment of MTrPs. Diagnosis of MTrPs will be determined by the presence of the following criteria: [1] hypersensitive point in a palpable taut band, [2] visible or palpable local spasm in response to MTrP palpation, and [3] reproduction of referred pain by palpation of the sensitive spot. These criteria have shown good interexaminer reliability (κ, kappa between 0.84 to 0.88) when applied by an experienced evaluator [20].

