### Randomization and blinding

At baseline, the non-interventionist physiotherapist, through the Random Allocation Software, will randomize by permuted blocks [4, 8], the participation of the 5 intervening physiotherapists with respect to a sample of 36 participants. The physiotherapist in charge of performing dry needling –which may be A (experimental) or B (control)- and 2 groups of 2 physiotherapists, G1 and G2, with an evaluator and a therapist in each group. 4 possible treatment groups (AG1, AG2, BG1, BG2) will be obtained evenly in each randomization block.

Participants who successfully pass the phone screening will be assigned a number on the randomization table in order of inclusion in the study; the treatment group (A or B) and physiotherapist group (G1 or G2) in which they will be included are specified. The physiotherapist responsible for carrying out the dry needling, will provide a list with the names of the participants, showing the type of intervention that each will receive (A or B).

Each participant will receive a single dry needling or sham dry needling intervention at the start of the first treatment session, conducted by a physiotherapist with more than 10 years of experience in MTrP treatment with dry needling. Said physiotherapist will be blinded to the baseline data of participants. On the other hand, both the physiotherapists who evaluate the participants and those who perform manual physiotherapy treatment and therapeutic exercise, will be unaware of the group of each participant.

In addition, data collected during the assessment of participants will not be revealed to the physiotherapists who perform the treatment, and participants will be instructed not to disclose their experience and information related to the first treatment session of dry needling.

Lastly, the physiotherapist responsible for the statistical analysis will be blinded. Once the intervention is finished he will receive a data table in excel with all the necessary data in binary code.

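### The number of muscles needled depends on palpation that the article does not place before the arm is known, and the arm-aware needling physiotherapist probably does the palpating

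*Protocol article*

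**What the plan says.** *Timing of allocation.* Under Randomization and blinding: "Participants who successfully pass the phone screening will be assigned a number on the randomization table in order of inclusion in the study". That number carries the arm.

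*Who knows the arm.* The same section ties the needling physiotherapist to a list of participant names "showing the type of intervention that each will receive (A or B". Of this clinician's own blinding it says only: "Said physiotherapist will be blinded to the baseline data of participants". The evaluators and the therapists giving manual treatment and exercise "will be unaware of the group of each participant", and the analyst is blinded too.

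*Which sites are treated.* The section on dry needling of myofascial trigger points contains three statements:
- on a muscle without a point: "If no MTrP is found during muscle palpation, the needling procedure will not be performed on that muscle"
- on the points to be treated: "The physiotherapist will treat each MTrP that have previously been located in the muscles"
- on the number per muscle: "At most one MTrP (the one producing most pain) in each of the muscles will be needled"

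Four muscles are named, with 12 insertions in each needled muscle. The control group is to have the same treatment with a sham needle.

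*Who looks for trigger points.* Under Participants, the examination is done "by a clinician with more than 10 years of experience in the treatment of MTrPs", using three stated diagnostic criteria.

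**The concern.** The sham is there so that the arms differ only in whether the needle penetrates. Contact, time and expectation should otherwise match, because the primary outcome is self-reported pain on a VAS. That requires the number of sites approached to be settled without regard to arm. If the person who judges whether a muscle contains a trigger point, and which point hurts most, already knows whether a real or a sham needle will follow, the search can be more or less thorough in one arm. The VAS comparison would then combine the effect of needling with a difference in how much procedure was delivered. This would be performance bias, and blinding the evaluators does not remove it.

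**Working it through.** The plan gives no figure on this point to reproduce. The check sets the relevant statements side by side and then adds simple arithmetic.

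**1. Order of events.** A number, and with it the arm, follows telephone screening. A telephone call cannot include palpation, so trigger-point judgements come after assignment.

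**2. Who knows the arm.** Among those who treat or assess, only the needling physiotherapist does. The wording about the list is unclear (this physiotherapist is said to provide it), but on any reading the list links names to arms, and whoever picks up a real or a sham needle knows which it is. The non-interventionist physiotherapist also knows the sequence but treats no one.

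**3. Who locates the points.** This is not stated. Three places bear on it:

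| Section | Description |
|---|---|
| Participants | The examiner is a clinician with over ten years in trigger-point treatment |
| Research team | One member of the seven is described with that experience |
| Randomization and blinding | The needling physiotherapist is described in the same terms |

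The examiner and the needler are therefore probably the same person. This is an inference.

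**4. Range of exposure.**
- Maximum: 4 muscles × 1 point × 12 insertions = 48 needle actions.
- Minimum: 0. The inclusion criteria accept areas of mechanical hypersensitivity as an alternative to active trigger points, while needling is omitted where no trigger point is found.

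**5. Could a count afterwards reveal an imbalance?** This is an illustration only; the detection rates and shifts are assumptions. Take 18 patients per arm, 4 muscles each, independent detection with probability p in one arm and p + d in the other.

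- Difference in mean sites = 4d; difference in needle actions = 12 × 4d.
- Standard error = √[4p(1 − p)/18 + 4(p + d)(1 − p − d)/18].
- Worked case, p = 0.6, d = 0.10: difference = 0.4 sites (4.8 actions); SE = √[4(0.24)/18 + 4(0.21)/18] = √0.100 = 0.32.

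| Shift d | Extra sites | Extra actions | SE for p = 0.4 / 0.6 / 0.8 | Difference ÷ SE, range over p |
|---|---|---|---|---|
| 0.05 | 0.2 | 2.4 | 0.33 / 0.32 / 0.25 | 0.6 to 0.8 |
| 0.10 | 0.4 | 4.8 | 0.33 / 0.32 / 0.24 | 1.2 to 1.7 |
| 0.20 | 0.8 | 9.6 | 0.33 / 0.30 / 0.19 | 2.4 to 4.2 |

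Under these assumptions a shift of 5 to 10 percentage points could not be told from chance at this sample size, while a shift of 20 points probably could. Counting sites is worth doing, but it does not replace locating the points before the arm is known.

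**The case against.** The strongest reply is that the article describes the points as already located when needling starts. A reader might infer from the palpation rule that the needler chooses the sites at session 1 with the arm in hand, but the article does not say so. That part of the reply stands. It does not settle the matter: the article names neither the person nor the time, and nothing puts the locating before disclosure. One could also read the phrase about order of inclusion as placing the numbering after the eligibility examination. Even so, the palpation in the needling section is not placed before the arm is known.

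Second, discretion is limited. There are three diagnostic criteria with a cited kappa of 0.84 to 0.88, four named muscles, one point per muscle, and a choice that follows the participant's own pain response. Both arms also receive the same information. All of this is correct and narrows the room for bias. But these limits cap the count without fixing it below the cap, and interexaminer agreement does not show that an examiner who knows the arm searches equally hard in both.

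Third, the needler's blinding to baseline data might be taken to mean that earlier findings cannot guide the choice of site. The documents do not support that. Trigger-point findings are not among the listed baseline items, and a needler who did the examination would know them anyway.

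Fourth, needled sites may well be recorded; an article need not say so. In addition, the blinded therapists look for trigger points in the same four muscles for pressure release (Table 1). That could serve as a cross-check if recorded, but it follows the needling in session 1, and real needling may itself change what is felt.

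**Conclusion.** The point holds as a gap in the design as written: the arm is fixed before palpation, the needler knows it, the site count depends on palpation, and no statement makes the locating of points precede knowledge of the arm. Exposure can vary from 0 to 48 needle actions per patient. That the arm-aware needler is also the person who locates the points is likely, because only one suitably experienced clinician is described, but it remains an inference.

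Two stronger conclusions are tempting and unsupported. One is that any imbalance would favour real needling: the document gives no basis for a direction. The other is a size in millimetres on the VAS: none can be derived, and the shifts tabulated in the check are assumptions. This is therefore an inexpensive improvement worth making, not a demonstrated bias.

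**What to change.** Replace the advance by-name list with release of the arm one patient at a time:

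1. The points are located, marked and recorded under the existing rule, with the arm undisclosed.
2. The non-interventionist physiotherapist, or a sealed envelope, then discloses that patient's arm.
3. The assigned procedure is applied to the marked points.
4. The numbers of marked and treated sites are reported by arm.

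State who locates the points and when. In the dry needling section, reconcile the sentence that has the points located beforehand with the rule for muscles where palpation finds none, and the wording on treating each located point with the limit of one per muscle. No needling rule needs to change for this purpose.

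The cost is 36 envelopes or messages, a sentence each in the randomization and needling sections, and about a minute per patient; no extra staff are needed. One weakness remains. If the bracketed figures after permuted blocks are block sizes of 4 and 8, with the arms balanced in each block, a needler who sees every past assignment could sometimes guess the next arm. The change reduces knowledge of the arm at the time of marking but does not guarantee its absence.

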### Manual physiotherapy and therapeutic exercise programme

Previous studies have shown that the inclusion of manual physical therapy in an exercise programme is more effective than exercise alone in reducing pain, increasing range of motion, strength and functionality [26, 27]. However, evidence has failed to show if an exercise mode is better than another, or which are the optimal frequencies or intensities thereof [27].

Treatment sessions will be implemented by two physiotherapists and divided into two parts; the first part will be based on manually treating the affected shoulder and the second part will be based on supervised therapeutic exercise. In addition, participants will be prescribed therapeutic home exercises, twice weekly (alternate days).

Manual physiotherapy treatment will last approximately 45 min. Techniques used in previous studies have been chosen for the treatment protocol, such as trigger point pressure release technique [28], longitudinal massage [28], scapulohumeral mobilization [19, 29], glenohumeral mobilization [19, 30], glenohumeral gliding and gapping [31–33] and mobilizations with active movement [34, 35]. The description and dosage of the techniques are contained in Table 1.

**Table 1 Tab1:** Physiotherapy intervention components

Treatment section	Dose
MTrP pressure realease technique On the most hyperalgesic point of the infraspinatus, upper trapezius, middle deltoids and subscapularis muscles. If there is no MTrP, the technique will be not applied to that muscle.	Twice on each point to be treated during 60 s and a 15 s rest.
Longitudinal massage Slow and deep massage along the muscle band of the hyperalgesic point treated above, with a tolerable pressure for the participant. If there is no hyperalgesic point, it will be applied to the entire muscle.	3 longitudinal sweeps across each taut band found, with an approximate duration of 20 s per sweep.
Scapular-humeral mobilizations Passive movements of ascent and descent, abduction and adduction, internal and external scapular rotation, scapular distraction movements and scapular circumduction of the affected shoulder.	10 repetitions of each movement, in the absence of pain or only slight discomfort tolerated by the participant. Participant in lateral decubitus of the healthy side.
Glenohumeral joint mobilizations Anterior and posterior passive movements of the glenohumeral joint. For the treatment position, the shoulder will be previously placed in passive abduction to end of ROM without pain.	2 sets of 20 anterior and posterior mobilizations. Participant supine.
Glenohumeral gapping and gliding Passive shoulder abduction to end range without pain. Subsequently, a technique of caudal gapping and gliding of the glenohumeral joint will be performed.	3 sets of 15 repetitions. Participant supine.
Mobilizations with active movement Slow and controlled active shoulder flexion movement to end range without pain. During the active movement, the physiotherapist will secure the scapula and will perform a posterolateral thrust on the humeral head.	3 sets of 5 repetitions in a sitting position. If there is pain, will find a plane of motion without pain or will change the position of the supporting hands.
Therapeutic exercise Performed during the treatment sessions and at home in 3 progressive stages, each lasting 2 weeks.	Sessions; once/week, 25 min with the physiotherapist’s supervision. At home; twice/week, 20 min.

The supervised therapeutic exercise will last approximately 25 min, which will be conducted in 3 progressive stages, 2 weeks each stage. Exercises used in previous studies have been selected such as scapulohumeral stabilization exercises [26, 29, 36], anterior [26] and posterior [37] flexibilization of the joint capsule, Codman exercises [26], proprioception, active and self-paced shoulder exercises [26], full-can exercise [26, 38], strengthening of the rotator cuff and scapular muscles [26, 39, 40]. The description and dosage of the exercises are set out in Table 2.

**Table 2 Tab2:** Description of the therapeutic exercises

Name and description	Dose	Weeks performed
Non-weight-bearing scapulohumeral stabilization exercise (CKC) Standing; 90° shoulder flexion and hands resting on the wall. Slow scapular movements down towards the midline of the back. The physiotherapist will give tactile stimuli for activation of the lower trapezius and serratus anterior. In the 3rd and 4th weeks, more weight will be placed on the arms by tilting the trunk.	3 sets × 8 reps 4 sets × 5 reps	1st & 2nd 3rd & 4th
Scapulohumeral stabilization (OKC) Standing; arms relaxed. Combined movements of lifting, retropulsion and lowering of both shoulders. During retropulsion and lowering should, shoulder blades should be stabilized in the dorsal midline.	3 sets × 10 reps	1st & 2nd
Anterior and posterior flexibilization of the joint capsule Anterior flexibilization; standing with hand and forearm leaning on a doorframe, the ipsilateral leg forward and the trunk tilted forward until a feeling an anterior stretching sensation, without pain. Posterior flexibilization, lateral decubitus of the affected side, shoulder and elbow at 90 degrees of flexion. From this position, the arm is brought towards the stretcher with the help of the other hand, until feeling posterolateral stretching without pain.	30 s × 3 times (each stretch)	1st & 2nd
Codman’s exercise Standing; trunk tilted forward with the unaffected arm supported on a high surface. Affected arm should be relaxed and fall freely. With the help of the unaffected hand, perform passive swing movements, avoiding muscle activation of the affected arm.	3 sets × 25 reps	1st & 2nd
Proprioception with a fitball Sitting, with the affected arm stretched and continuously supported on the fitball, perform side, anterior and diagonal movements, helping by tilting the trunk. 2nd set with closed eyes. 3rd set with destabilization thrusts on the fitball.	2 reps each movement. Until completion of 1 set.	1st & 2nd
Self-paced shoulder flexion and abduction Standing; hands apart at shoulder level, holding a wooden stick. Flexion; arms extended to AROM without pain, in a controlled manner. Abduction (affected side); arms extended to end range without pain arms, in a controlled manner. If there is discomfort or lack of strength during the exercises, complete the ROM with the help of the other arm. On the descent of both movements, scapular control will be required.	3 sets × 8 reps (each movement)	3rd & 4th
Active shoulder flexion using a fitball Standing; hands resting on a fitball against the wall and leaning forward. Active flexion movements alternating both arms, rolling the fitball along the wall to reach the maximum flexion of the affected shoulder without pain.	3 sets × 6 reps	3rd & 4th
Full-can Standing; arms stretched at 90° abduction and 30° horizontal flexion. External rotation movements of the shoulder and lowering of the scapula.	4 sets × 10 reps	3rd & 4th
Scapulohumeral stabilization using weights (OKC) Standing; leaning against the wall. Horizontal bending movements (from 90° to 0°) holding a dumbbell of 0.5 or 1 kg according tolerance in each hand. During movement take both scapulae to the midline of the back in a controlled manner.	3 sets × 8 reps	5th & 6th
Strengthening of the rotator cuff and scapular muscles (Theraband) Flexion, extension and abduction; in the standing position, with the arm extended and holding the band with the hand of the affected arm and holding the other end with the ipsilateral foot, will perform the exercises: [1] flexion, [2] extension and [3] abduction to end AROM without pain. During the abduction return movement, the patient will be instructed to control the internal rotation and scapular adduction movement. External and Internal rotation; in the standing position, with a towel between the body and the affected arm, shoulder at 0° flexion and elbow at 90° flexion, gripping the band with the hand of the affected arm and securing the other end to the doorknob, will perform the exercises: [4] external rotation and [5] internal rotation to AROM without pain.	Flex. & Abd.; 3 sets × 8 reps // Ext., Rot. Ext. & Int.; 3 sets × 10 reps	5th & 6th

Therapeutic exercises at home will last 15 to 20 min or so. Exercises will perform twice per week (alternate days) and for which the physiotherapist will provide the guidelines and training in the treatment sessions.

The exercises will comprise 3 progressive stages as mentioned above, following an information sheet with the relevant instructions for each exercise. In each treatment session participants will be asked about the exercises performed at home, to learn about any difficulties encountered and make the necessary corrections. Participants will be instructed to continue performing therapeutic exercises at home once the intervention is completed and until the last evaluation (at 6 months post-treatment).

Participants will not receive any physiotherapy or medical treatment for shoulder pain during the study intervention. Should any adverse event occur during the execution of the dry needling, or at any time during the intervention in the study, participants will discontinue participation.

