### Statistical analysis

Data analysis will be carried out following the evaluation standards of the design of experimental studies with a control group. The experimental group (dry needling + manual physiotherapy and therapeutic exercise) will be compared with the control group (sham dry needling + manual physiotherapy and therapeutic exercise).

Data will be analysed using SPSS v.22 software for Windows. All statistical tests will be carried out considering a confidence interval of 95% (*p*-value <0.05) to determine the effectiveness of the 2 interventions by the method of intention to treat. Prior to statistical comparisons, all data will be analysed to determine the distribution of normality by the Shapiro-Wilk test. Subsequently, the homogeneity of the two intervention groups will be studied using Student’s t test for independent samples for data conforming to normal and the Mann-Whitney test for data that do not. The sex variable will be studied through Pearson χ2 or Fisher’s exact test, if the former cannot be used. Then a descriptive analysis of the data for the dependent variables will be performed. In these analyses, the mean and standard deviation (SD) for the dependent variables with normal distribution will be calculated. For variables that do not conform to normal, the data will be expressed with the median and first and third quartiles.

For the sex variable, frequencies are used. The existence of differences within each group will be determined, taking into account each group in isolation, between the different measurements (baseline and one week after dry needling; and post-treatment: at one week, at one month, at 3 months and at 6 months) in each of the study variables. In the VAS variable, measurements will also be taken in the treatment sessions; 2nd week, 3rd week, 4th week, 5th week, 6th week, using ANOVA for repeated measures, supplemented with simple and Helmert-type contrasts for variables that follow normal or Friedman’s ANOVA test, supplemented by Dunn’s multiple comparison test for those variables that will not conform to normal. ANCOVA will be performed to see the effect through different analyzes of the results and to intensify statistical power of the study. For this, the existence of a linear relationship and the homogeneity between the crude and basal scores of the dependent variables will be previously studied.

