For comparison between groups, a variable that we define as “difference” will be found; for each dependent variable, by subtracting the baseline measurement - at one week following needling, baseline - post 1 week, baseline - post 1 month, baseline - post 3 months and baseline - post 6 months (for the DASHe variable, the measurement will not be collected at one week after needling).

For the VAS variable, the “difference” variables will be found between baseline - week 2, week 3, week 4, week 5, week 6. To determine differences in dependent variables between the two intervention groups, the Student t test will be applied for related samples in variables whose data follow normal, in this case the effect size will be calculated according to the formula d = 2 t/√g. In the case of variables whose data do not follow normal, an analysis by the Mann-Whitney test will be performed and the effect size will be estimated according to Grissom procedures according to the formula.

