## Discussion

This protocol will be carried out for a randomized single-blind clinical trial, in order to investigate whether the inclusion of dry needling in a manual physiotherapy and therapeutic exercise programme has a greater effect in reducing pain and disability in subjects with chronic shoulder pain of unspecific origin.

Chronic shoulder pain is a complex painful condition, with no clear clinical definition [3], whose high recurrence and persistence of symptoms [1, 2], make it difficult to choose the most appropriate treatment. Also a relationship has been shown between high prevalence of myofascial trigger points in the shoulder muscles and the presence of pain [1, 3, 13, 14], so these patients could benefit from an approach focused on muscle treatment.

Moreover, previous studies have shown the efficacy of the combination of manual therapy techniques and therapeutic exercise for shoulder pain, although the best frequency and dosing are not clear [5, 17]. The use of dry needling is recommended in patients with Myofascial Pain Syndrome of the Upper Quadrant [4], while the benefits of a single session of dry needling in a multimodal programme has been observed in cases of post-surgical shoulder pain [19].

Moreover, the benefits of therapeutic exercises in cases of shoulder pain [26, 36], show the importance of including them in the implementation of this protocol, not only during treatment sessions but also at home. Among the exercises included in this protocol, scapular training is a fundamental aspect, as a reduction in electromyographic activation in the serratus anterior and lower trapezius has been observed in patients with shoulder pain, as well as greater activation of the upper trapezius, reflected in a scapulohumeral muscle imbalance [36].

Thus, and based on the literature, we selected different techniques of manual physiotherapy and therapeutic exercise for the creation of this intervention protocol, which also includes a single session of dry needling or sham dry needling to study its potential benefits. Being techniques with few adverse effects and being cheaper in terms of cost-effectiveness, it may be an alternative to more aggressive interventions such as surgery and infiltrations for which similar short-term results have been obtained [51].

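### Any adverse event during the six-week intervention ends study participation as worded, so those patients lose every post-treatment VAS and every post-baseline DASH value; the likely bias is small and the wording is easy to mend

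*Protocol article*

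**What the plan says.** The rule closes the section Manual physiotherapy and therapeutic exercise programme of the protocol article: if "any adverse event occur during the execution of the dry needling, or at any time during the intervention in the study, participants will discontinue participation". It is not graded by severity, seriousness or relation to treatment, and what it ends is participation.

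The timing comes from three places. Interventions gives six weekly sessions, "with a corresponding evaluation before the start of each treatment session", and then assessments 1 week, 1 month, 3 months and 6 months after the last session. Randomization and blinding places the single real or sham needling "at the start of the first treatment session". Table 3 schedules VAS at every visit, but DASH only at baseline and at the four post-treatment visits. Statistical analysis confirms this: "for the DASHe variable, the measurement will not be collected at one week after needling".

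On analysis, the tests are meant "to determine the effectiveness of the 2 interventions by the method of intention to treat", and the groups are compared on baseline minus each later visit. The article gives no adverse event rates. The Discussion describes the treatments in the words "Being techniques with few adverse effects".

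**The concern.** Intention to treat asks for outcomes on everyone randomised, whether or not they completed treatment. A rule that removes patients from the study, and not only from treatment, stops outcome collection for a reason that arises after randomisation. That reason may be related to the treatment under test. Manual therapy and exercise are the same in both arms, so the only planned difference is the needling. At least one muscle must be affected ("with pain reproduced in one or more muscles"), and the procedure states that "Needle insertion will be repeated 12 times in each muscle", against a placebo needle in the control arm.

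If events were more frequent in one arm and the patients concerned did worse or better than the rest, the remaining patients would no longer be a fair comparison. The allowance for losses in the sample size section protects numbers, not against selective loss. A later analysis plan can decide how to treat missing values, but it cannot recover visits that the protocol has cancelled.

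**Working it through.** The plan gives no figure of its own for this loss, so the check has two parts: a count of visits, and a bias calculation on stated assumptions.

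**1. Values lost, from Table 3.** Scheduled post-baseline values are VAS 5 + 4 = 9, DASH 4, dynamometry 1 + 4 = 5, goniometry 1 + 4 = 5 and algometry 2 + 4 = 6. Each evaluation precedes its session, so a patient who leaves at session k keeps k − 1 of the 9 VAS values.

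| Event at session | VAS kept (of 9) | Post-treatment VAS kept (of 4) | DASH kept (of 4) | Dynamometry, goniometry kept (of 5 each) | Algometry kept (of 6) |
|---|---|---|---|---|---|
| 1 | 0 | 0 | 0 | 0 | 0 |
| 2 | 1 | 0 | 0 | 1 | 1 |
| 3 | 2 | 0 | 0 | 1 | 2 |
| 4 | 3 | 0 | 0 | 1 | 2 |
| 5 | 4 | 0 | 0 | 1 | 2 |
| 6 | 5 | 0 | 0 | 1 | 2 |

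Whenever the event occurs in the six weeks, 0 of 4 post-treatment VAS and 0 of 4 DASH values remain. The change scores for those visits cannot be formed from observed data.

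**2. Difference in exposure between arms.** With 12 insertions per muscle and one to four muscles, real needling means 12 × 1 = 12 to 12 × 4 = 48 insertions. A higher event rate with real needling is possible, but the article does not show one.

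**3. Size of the bias.** Assumptions, none from the documents: complete-case analysis; leavers improve 10 to 20 mm less on VAS and 5 to 10 points less on DASH than patients who stay; the same deficit in both arms. Then

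bias = (event rate, real − event rate, sham) × deficit.

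- Equal rates: 0.
- 10% and 5%: VAS 0.05 × 10 to 20 = 0.5 to 1.0 mm; DASH 0.05 × 5 to 10 = 0.25 to 0.5 points.
- 20% and 5%: VAS 0.15 × 10 to 20 = 1.5 to 3.0 mm; DASH 0.15 × 5 to 10 = 0.75 to 1.5 points.

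With 18 per arm, each excess leaver moves the difference by 10/18 to 20/18 = 0.56 to 1.11 mm on VAS and by 5/18 to 10/18 = 0.28 to 0.56 points on DASH.

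If the deficit differed by arm, equal rates would not give exactly zero. For example, 5% in each arm with deficits of 20 and 10 mm gives 0.05 × 20 − 0.05 × 10 = 0.5 mm, still small.

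**4. Against the minimal differences in the article.** These are 13 mm for VAS and 10.2 points for DASH. A 13 mm bias needs 13 ÷ (20/18) = 11.7, so 12 excess leavers of 18, at a 20 mm deficit. At 10 mm it needs 13 ÷ (10/18) = 23.4, which is impossible with 18. For DASH at a 10-point deficit, 10.2 ÷ (10/18) = 18.4, also more than 18.

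**5. Numbers lost.** 18 × (0.10 + 0.05) = 2.7 patients, or 18 × (0.20 + 0.05) = 4.5 patients. The stated figures leave 36 − 28 = 8 for losses of every kind.

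**The case against.** The strongest reply is that the sentence was meant to stop treatment only. It stands in the treatment section, directly after a rule on concomitant care, and does not say that assessments cease. The article condenses a fuller protocol, and follow-up of patients who stop treatment is the kind of detail that may stand there. This reading is possible, and it would reduce the point to unclear wording. It does not remove it. The sentence names participation, and just before it the article separates the end of the intervention from the last evaluation, so the narrower term was available. Staff who follow the text would release the patient.

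Four stronger readings are tempting, and the documents do not support them:

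- That the rule contradicts intention to treat. It does not, since patients can still be analysed in the group to which they were assigned.
- That the missing values could only be imputed. A likelihood-based repeated-measures model can use the earlier weekly VAS values without imputation. DASH has no on-treatment value to help, so it is the more exposed measure.
- That harmed patients disappear from the record. Nothing says that adverse events go unrecorded or unreported; what is lost is later outcome values.
- That the result would be biased towards needling. The article gives no event rates and no outcomes for leavers, and expects few adverse effects. The sign reverses if sham loses more patients or if leavers do better.

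**Conclusion.** The point holds as a minor one. As worded, any adverse event in the six weeks ends study participation, no provision for continued assessment is stated, and the patient is left with none of the four post-treatment VAS values and none of the four post-baseline DASH values. This is avoidable missing data, possibly related to arm, and it works against the stated intention-to-treat aim.

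The consequence is conditional and probably small: 0 to 3.0 mm on VAS and 0 to 1.5 points on DASH over the ranges tried. All of this rests on assumed event rates, assumed deficits and a complete-case analysis that the plan does not state. The VAS figures would be smaller if earlier weekly values were used. The rule could not plausibly produce a clinically relevant difference by itself. The assumed losses fit within the planned allowance, although that allowance must also cover all other dropout.

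**What to change.** Keep the safety stop for any adverse event, but change what is stopped. The sentence should say that the participant discontinues the study treatment, that all assessments scheduled in Table 3 (VAS, DASH, dynamometry, goniometry and algometry) continue to 6 months unless consent is withdrawn, and that the participant is analysed in the assigned group. Report treatment discontinuations and their reasons by arm.

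The missing-data argument gives no ground for loosening the safety rule itself, for instance by stopping only the component thought to have caused the event. The treating therapists are blinded to group and could not easily attribute an event to needling.

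The cost is a minor amendment to a protocol with ethics approval, and follow-up contacts with participants who have stopped treatment. The visits are already in the schedule. If treatment-only discontinuation was always intended, the same edit serves as a clarification.
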